#### Qualitative evaluation

Semi-structured interviews will be carried out with a purposively selected sub-sample of students (*n* = 30) who participated in the program to examine their experiences of the program and its impact on their knowledge, understanding, confidence and capabilities. The sample will include students selected from regional and metropolitan areas and varied levels of participation (from non-completion to full completion). Interviews will be carried out face to face and by telephone, audio recorded and transcribed verbatim. Data will be analysed thematically using Framework Analysis.

### II. Evaluation among teachers and community health workers

#### Quantitative evaluation

Intervention teachers will be asked to comment on and rate the teaching resources using a 5 point Likert scale (very good – very poor) with space for additional comments. This measure is included within the teaching manuals and is intended to be completed following each lesson.

#### Qualitative evaluation

Telephone interviews will be conducted with all intervention teachers and community health workers, and a subset of standard LLN teachers, on completion of the program. The interviews will explore their experiences and views on the content, delivery and success of the program, challenges faced, suggestions for improvement and how adult literacy teachers and health professionals worked together to deliver the program. Standard LLN teachers will be asked about experiences with the class and possibilities for contamination. As before interviews will be audio recorded, transcribed verbatim and thematically analysed.

#### Statistical analysis

The primary analysis will be by intention to treat. We will compare outcomes between the intervention and standard LLN arms for the primary outcome using a regression analysis that will account for clustering using appropriate methods [52]. We will use linear, logistic or ordinal logistic regression analyses as appropriate.

We will also conduct secondary analyses that adjust for baseline scores on the measures (where available), and health literacy and numeracy (measured with NVS). We will conduct these analyses separately. We will also conduct the same set of analyses for the primary outcomes, but using the intervention as actually received.

The statistician will be blinded to the allocated group definitions (i.e., health literacy vs standard LLN) until completion of the statistical analysis.

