### Sample size

The primary outcome for sample size calculation is the functional health literacy score used in our pilot study ([41]). We estimate that 86 students are required per group to detect a difference in the mean total score between the intervention and standard LLN groups of 0.5 standard deviation (SD) with 90 % power at the two-sided 5 % significance level. An established systematic review indicates that a half-standard deviation is the ‘threshold of discrimination’, or the minimally important difference, for changes to psychosocial outcomes in chronic disease assessment [42]. To allow for clustering within a class and using an intra-cluster correlation coefficient of 0.05 and an average class size of 10, the required sample size is 125 students. Allowing for 15 % loss to follow-up, we aim to recruit 150 participants in each arm (*n* = 300 in total; 15 pairs of classes of approximately 10 students per class). This sample size will also be sufficient to detect a difference in retention of at least 20 % between the intervention and standard LLN group, with 80 % power. Due to the unpredictability of TAFE enrolments, unequal cluster sizes are assumed.

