### I. Evaluation among students

#### Quantitative evaluation

##### Baseline measures

Include demographic and health literacy screening questions. Demographic information includes age, sex, country of birth, language spoken at home, and self-reported health status.

Health literacy includes: the Single Item Literacy Screener (SILS) “How often do you need to have someone help you when you read instructions, pamphlets, or other written material from your doctor or pharmacy?” [43]; self-report of reading ability “How would you rate your ability to read” [44], using a cut off of 3 “sometimes”/”okay” to denote poor literacy; Newest Vital Sign (NVS) [45] with minor modification to the food units presented in the stimulus to make it suitable for use in Australia.

We will take baseline measures of the main primary and secondary outcomes: functional health literacy skills (described below and in Additional file 1), confidence, and components of the Health Literacy Questionnaire (HLQ), described below.

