##### Immediate post intervention outcomes

The primary outcome of functional health literacy skill will be assessed using a purpose designed measure informed by the intervention course core content (see Additional file 1):How to use a thermometer (score range 0–3).Interpretation of a medicine labels, (score range 0–5).Interpretation of a food label, 9 items (score range 0–10; not assessed at baseline).

Knowledge scores will be calculated using a marking scheme developed a priori (see Additional file 2). Health skills tasks will be assessed separately, as well as a combined outcome, which will be a weighted sum of the components.

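### The primary comparison is unadjusted although baseline skills scores and NVS are scheduled: valid and adequately powered, but it gives up precision at almost no saving

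*Protocol article*

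**What the plan says.** The Statistical analysis section of the protocol article sets an intention-to-treat comparison of the arms "for the primary outcome using a regression analysis that will account for clustering using appropriate methods". No covariates are named. The next paragraph adds "secondary analyses that adjust for baseline scores on the measures (where available), and health literacy and numeracy (measured with NVS"), and says that these analyses are run separately. All covariate adjustment therefore sits below the primary analysis.

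The covariates are part of the planned data collection. The Baseline measures section says "We will take baseline measures of the main primary and secondary outcomes" and lists functional health literacy skills among them. The same section and Table 2 place the NVS at baseline. There is one gap: under Immediate post intervention outcomes, the food-label task (0 to 10) is marked "not assessed at baseline". Only the thermometer task (0 to 3) and the medicine-label task (0 to 5) have a baseline score. The combined primary score is described as a weighted sum of the three.

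The Sample size section plans 15 matched pairs of classes of about 10 students. Its calculation contains no allowance for covariate adjustment.

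**The concern.** Baseline performance on the same tasks, and a general health literacy and numeracy score, are the obvious predictors of the post-intervention skills score. Leaving them out of the primary model puts the variation they explain into the standard error.

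Only 30 classes are randomised. If the arms happen to differ in starting skill, part of that difference passes into the unadjusted estimate, which is the trial's headline result. The adjusted result, which may be more precise and would allow for the realised difference, is labelled secondary. If the two differ, the less precise one stands as the answer.

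The word separately is also open to two readings. If it means one covariate set per model, no planned model uses the baseline skills scores and the NVS together. The NVS matters here because, like the food-label task, it uses a food-based stimulus, and that task has no baseline of its own.

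**Working it through.** **Inputs from the Sample size section.** Target difference, power and significance level: "0.5 standard deviation (SD) with 90 % power at the two-sided 5 % significance level". The stated number before clustering is 86 per group. The clustering step reads "intra-cluster correlation coefficient of 0.05 and an average class size of 10, the required sample size is 125 students". Recruitment is then set at 150 per arm, with losses of 15% expected. There are 15 classes per arm.

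**Input not in the document.** The baseline-outcome correlation r is assumed, with range 0.3 to 0.6.

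**1. Reproducing the plan's figures.**
- Per group without clustering: 2 × (1.960 + 1.282)² / 0.5² = 84.1, so 85 by the normal approximation. The t-based solution is 85.03, so 86.
- Design effect: 1 + (10 − 1) × 0.05 = 1.45. Then 86 × 1.45 = 124.7, so 125.
- Loss to follow-up: 125 / 0.85 = 147.1, so 148, rounded to 150 (15 classes of 10).

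The figures reproduce, for an unadjusted comparison.

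**2. Chance baseline difference, ignoring any gain from matching.**
- SE = √(2 × 1.45 / 150) = 0.139 SD.
- 1.96 × 0.139 = 0.27 SD.
- Chance of a difference above 0.2 SD in either direction: 0.2 / 0.139 = 1.44, so about 15%. Above 0.25 SD: about 7%.
- If the intra-cluster correlation were 0.10 (assumed): SE = √(2 × (0.10 + 0.90/10) / 15) = 0.159 SD, and the two chances are about 21% and 12%.

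**3. Effect of a baseline difference on the unadjusted estimate.** The expected shift is r times the difference. For a 0.27 SD difference, which is a 95% limit and not a typical value:
- r = 0.3: about 0.08 SD
- r = 0.5: about 0.14 SD
- r = 0.6: about 0.16 SD

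The target effect is 0.5 SD.

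**4. Precision from adjustment.** If r is the same at student and class level, the variance is multiplied by 1 − r². The table assumes 15 classes per arm, 8.5 students analysed per class (10 × 0.85) and 28 degrees of freedom.

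| r | Variance cut | SE of difference (SD) | Power for 0.5 SD |
|---|---|---|---|
| unadjusted | none | 0.147 | 91% |
| 0.3 | 9% | 0.140 | 93% |
| 0.5 | 25% | 0.127 | 97% |
| 0.6 | 36% | 0.117 | 98% |

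**5. Sensitivity to the equal-correlation assumption.** If the covariates explain only variation between students within classes, the class component (0.05) stays and only 0.95 / 8.5 = 0.1118 shrinks.
- r = 0.3: (0.05 + 0.1118 × 0.91) / 0.1618 = 0.94, a 6% cut.
- r = 0.6: (0.05 + 0.1118 × 0.64) / 0.1618 = 0.75, a 25% cut.

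**The case against.** The strongest reply is that nothing in the plan is invalid. A cluster-aware intention-to-treat comparison of post-intervention scores is unbiased over randomisation, and its standard error already includes chance baseline differences. The wider interval and the exposure to imbalance are therefore one cost seen from two sides. The sample size was calculated for this analysis and reproduces, with about 91% power after the planned loss. All of this stands. A reader might infer that the primary result would be biased or the trial underpowered, and the document supports neither.

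A reader might also infer from the small number of classes and the mixed population in the Background that imbalance is likely. That goes too far. The chance of more than 0.2 SD is about 15% before any credit for matching. The Study design and Inclusion criteria sections match classes on course code, language mix, English proficiency, literacy skills and region. Students are restricted to one skills level, and at larger metropolitan campuses with more than one participating class they are randomised to classes individually. Matching on typical class profiles is not adjustment for measured scores, so some exposure remains, but it is probably smaller than the figures above.

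The gain is also assumed. No correlation is given, two short scales and the NVS may predict the combined score only modestly, and the food label has no baseline. Its 10 of 18 raw points (3 + 5 + 10) is not its share of a weighted sum.

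Finally, the protocol does not promise complete baseline data. Assessments are spread over several teaching sessions, so gaps are plausible, and a primary model that needs no baseline data has some appeal. A simple rule for missing covariates meets that point.

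The absence of a separate analysis plan does not remove the concern, because the article itself places adjustment among the secondary analyses.

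**Conclusion.** The point holds as an efficiency improvement. It does not correct an error. The plan makes a valid, adequately powered, unadjusted comparison primary, when covariates already scheduled for collection could make it more precise and less dependent on the baseline balance that happens to occur.

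The variance reduction is about 9% to 36% for an assumed r of 0.3 to 0.6 acting equally at student and class level, and about 6% to 25% if it acts only within classes. The imbalance figures (SE 0.139 SD, about a 15% chance of exceeding 0.2 SD) rest on an intra-cluster correlation of 0.05 and 10 students per class, and give no credit for matching. For the combined score, the gain may fall toward the lower end or below it, because its food-label part can be predicted only indirectly.

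**What to change.** State one primary model: a cluster-aware regression of the post-intervention combined score on arm, adjusted jointly for baseline thermometer score, baseline medicine-label score and NVS, and reflecting the matched-pair design. Say that the food-label task has no baseline and that the NVS serves as its nearest available proxy.

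Pre-state a simple method for missing baseline covariates, such as filling in the mean over both arms, so that no student with an outcome is dropped for lack of a baseline value. Keep the unadjusted comparison as a sensitivity analysis, and say that the adjusted model decides the primary conclusion.

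The cost is a few sentences in the analysis section, fixed before the statistician sees outcome data. No new data collection is needed, and the sample size can stay as it is.

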#### Quality assurance

Data will be collected on paper-based questionnaires and entered into a central computerised database. Ten percent 10 % of records will be manually checked against the paper copies. For knowledge items that require coding and scoring, double-marking will be conducted to ensure consistency.

#### Project reference committee

A cross-sectoral reference group will oversee the research, comprising representatives from partner organisations (National Prescribing Service, Clinical Excellence Commission, NSW Health, TAFE NSW), the Chief/Partner Investigators, and NSW Health Literacy Network, a national group chaired by the NSW CEC involving state and national stakeholders from health, adult education, and consumer representatives; and external experts in health and adult education. The target group (i.e. adult learners with low literacy) will be represented by an appointed ‘consumer representative’ and by being actively involved in the development of the health literacy program to ensure the content and structure of the program is tailored to their needs, preferences and skill level.

#### Expected outcomes of the study

This research aims to develop and evaluate a novel adult health literacy training program to improve both language, literacy, and numeracy skills, together with specific health literacy competencies among socially disadvantaged Australian adults. It will assess the achievement of key literacy and health literacy outcomes when delivered under “real life” conditions at selected Australian adult education centres, and provide evidence on how the program can be implemented in varied circumstances. There is no existing model for collaboration in Australia between statutory adult education and public health organisations that systematically addresses both health and education outcomes. This project will enable us to test this cross-sector collaboration and provide high quality data to inform both education and health policy decisions.

## Discussion

This study seeks to demonstrate effectiveness of a health literacy program embedded in an adult basic education setting, in improving both health literacy and adult education outcomes. In the process of doing so, it seeks to build partnerships between health and education agencies to find new ways to deliver targeted health messaging to these difficult-to-access populations. The evaluation trial will provide insight into translating and scaling up health literacy education for vulnerable populations with low literacy, including linguistically and culturally diverse adults, and durability of any observed gains. We hope that the results of this trial will influence policy makers to open pathways for health and education agencies to work together to serve the needs of these disadvantaged populations – which may reduce some of the costs to the community of limited health literacy.

### Registration details

The trial is registered with the Australian New Zealand Clinical Trials Registry (registration no. ACTRN 12616000213448).

## Abbreviations

ACSF: Australian Core Skills Framework
CALD: culturally and linguistically diverse
CEC: Clinical Excellence Commission
FCE: Functional Context Education
HLQ: Health Literacy Questionnaire
LLN: language, literacy, and numeracy
NESB: non-english speaking background
NPS: National Prescribing Service
NSW: New South Wales
NVS: Newest Vital Sign
REALM: Rapid Estimate of Literacy in Medicine
SILS: Single-Item Literacy Screener
TAFE: Technical and Further Education
TOFHLA: Test of Functional Health Literacy in Adults
UK: United Kingdom
US: United States
